## Abstract

**Background:**

Despite an overwhelming body of evidence showing the benefits of physical activity (PA) and exercise for cancer survivors, few survivors meet the exercise oncology guidelines. Moreover, initiating, let alone maintaining exercise programs with cancer survivors continues to have limited success. The aim of this trial is to evaluate the influence of peer support on moderate-to-vigorous PA (MVPA) and various markers of health 12 months following a brief supervised exercise intervention in cancer survivors.

**Methods:**

Men and women previously diagnosed with histologically-confirmed breast, colorectal or prostate cancer (*n* = 226), who are >1-month post-treatment, will be invited to participate in this trial. Once enrolled, participants will complete 4 weeks (12 sessions) of supervised high intensity interval training (HIIT). On completion of the supervised phase, both groups will be provided with written recommendations and verbally encouraged to achieve three HIIT sessions per week, or equivalent exercise that meets the exercise oncology guidelines. Participants will be randomly assigned to receive 12 months of peer support, or no peer support (control). Primary and secondary outcomes will be assessed at baseline, after the 4-week supervised HIIT phase and at 3-, 6- and 12-months. Primary outcomes will include accelerometry-derived MVPA and prescribed HIIT session adherence; whilst secondary outcomes will include cardiorespiratory fitness ($$ \dot{\mathrm{V}}{\mathrm{O}}_{2\mathrm{peak}} $$), body composition, quality of life and select cytokines, myokines and inflammatory markers. Random effects mixed modelling will be used to compare mean changes in outcomes between groups at each time point. A group x time interaction will be used to formally test for differences between groups (alpha =0.05); utilising intention-to-treat analyses.

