### Primary outcome

#### Moderate-to-vigorous physical activity

The primary outcome for this study will be MVPA at 12 months. MVPA can be accrued through performance of the prescribed HIIT sessions and/or by engaging in any MVPA. Daily physical activity will be assessed through the use of training diaries, retrieval of HR and Wattbike ergometer data from each training session, as well as Actigraph GT3X+ accelerometry (Pensacola, Florida). Participants will be asked to wear an accelerometer on an elastic waist belt aligned with the right anterior axillary line for 7 days immediately preceding baseline, 3-, 6- and 12-month assessments. Participants will be asked to complete a brief log to record when they wear the monitor, including wake and sleep times and if they removed the monitor for > 10 min. They will be instructed to wear the device at all times, excluding sleep, any water-based activities (e.g. showering/swimming) and contact sports. Accelerometers will be initialised with 30 s epochs and a 30 Hz sampling frequency. A valid day will be defined as a minimum wear-time of 10 waking hours, with non-wear time defined as 60 min or more of consecutive activity counts of zero. For activity data to be included, participants must satisfy a minimum wear-time criterion of at least four of the 7 days, with at least one of the days being a weekend day [44, 45]. Minutes of MVPA will be calculated using Actilife v6 (Pensacola, Florida) and the cutpoints described by Troiano et al. [44].

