### Statistical considerations and data analysis

A priori power calculations determined that a sample of *n* = 188 (*n* = 94 per group) will be needed to detect a minimum between-group difference in MVPA levels at 12 months, with 80% power and 5% alpha. To account for an anticipated dropout rate of 20%, 226 participants (*n* = 113 per group) will thus be recruited for this study. A priori criteria for successful provision of peer support will be contacting participants on average on one or more occasions per week over the 12-month maintenance phase.

Data will be assessed for normality of distribution using the Kolmogorov-Smirnov test. Raw continuous data (e.g. minutes of MVPA per day) will be analysed using linear mixed (fixed and random) modeling, to assess changes over time and differences between groups. Group, time, and group × time interaction will be treated as fixed factors; participants will be treated as a random factor with individual intercepts. Each model will include covariates, as appropriate, and will be adjusted using the baseline value as a fixed continuous covariate as previously described by Courneya et al. [113]. Model residuals will be formally assessed for normality by use of the Kolmogorov-Smirnov test and visual inspection of histogram plots. Bonferroni pairwise adjustments will be made for all subsequent comparisons.

Non-continuous data will be analysed with the target distribution and relationship fixed to multinomial logistic regression. Statistical significance will be set at an alpha of *p* < .05 and analyses will be conducted using the intention-to-treat approach. There are no interim analyses planned or early trial termination guidelines. Data from the peer supporters will be analysed separately to those of the participants.

Qualitative data from the semi-structured interview transcripts will be assessed using inductive thematic analysis. Codes will be assigned to salient text segments across the entire data set, before codes will be combined to define overarching themes [108].

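### The named formal test is the group-by-time interaction, but the primary outcome and the sample size concern the 12-month group difference in MVPA, which no stated test addresses at 5%

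*Protocol article*

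**What the plan says.** - **Formal test** (Abstract, Methods): "A group x time interaction will be used to formally test for differences between groups (alpha =0.05". The sentence before it says that the mixed model will compare the groups' mean changes at each time point.
- **Primary outcome** (Primary outcome, Moderate-to-vigorous physical activity): "The primary outcome for this study will be MVPA at 12 months".
- **Sample size** (Statistical considerations and data analysis): the stated purpose of the calculation is "to detect a minimum between-group difference in MVPA levels at 12 months". It gives 94 evaluable participants in each arm, 188 in all, for power of 80% at the 5% level.
- **Model** (same section): group, time and their interaction as fixed factors, a random intercept per participant, and each model "adjusted using the baseline value as a fixed continuous covariate".
- **Multiplicity** (same section): "Bonferroni pairwise adjustments will be made for all subsequent comparisons". The 12-month contrast is not exempted.
- **Visits with MVPA**: the primary-outcome section has the accelerometer worn before the baseline, 3-, 6- and 12-month assessments. Table 1, the Outcomes section and the abstract also place the primary outcome at the end of the supervised phase. Randomisation follows that visit (Randomisation section).

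**The concern.** An interaction test asks whether the gap between groups changes across the levels of time. The trial's hypothesis is that there is a gap at 12 months. These are different null hypotheses. The interaction can be significant when the 12-month gap is zero, and it can be null when the gap is present and constant. In a maintenance trial a constant gap is a success.

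The only test called formal, at the 5% level, is the interaction. The comparison that the trial was sized for falls among the follow-on comparisons, where the Bonferroni rule departs from the 5% used in the power calculation. At stake is which result lets the trial be called positive.

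**Working it through.** **Inputs.** From the article: 94 evaluable per group, 80% power, 5% alpha, 1:1 allocation, random-intercept model, baseline as covariate. Not given, so assumed: a two-sided test; a within-person correlation ρ of 0.3 to 0.7; the size of the Bonferroni family. The article gives no target difference or SD, so 188 cannot be rebuilt directly and the effect must be back-solved.

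**Step 1: the implied effect.** d = (1.960 + 0.842) × √(2/94) = 0.409 by the normal formula, or 0.411 by the t-test. I use 0.41, which returns 94 per group.

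**Step 2: power of the interaction.** With n = 94 per arm and group differences δ_t (in SD units) at T levels, the noncentral F has T − 1 numerator degrees of freedom and noncentrality

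λ = (n/2) × Σ(δ_t − mean δ)² / (1 − ρ).

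*Faded benefit, levels 3, 6 and 12 months:* δ = (0.41, 0.205, 0), mean 0.205, sum of squares 2 × 0.205² = 0.0841. So λ = 47 × 0.0841 / (1 − ρ) = 5.6, 7.9 and 13.2 at ρ = 0.3, 0.5 and 0.7.

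*Sustained benefit, same levels:* δ = (0.41, 0.41, 0.41), sum of squares 0, so λ = 0 and the rejection rate is 5% at any ρ.

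*Sustained benefit with one pre-randomisation level:* δ = (0, 0.41, 0.41, 0.41), mean 0.3075, sum of squares 0.3075² + 3 × 0.1025² = 0.1261. So λ = 8.5, 11.9 and 19.8.

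Proportion of trials with a significant interaction:

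| Levels of time | Benefit | ρ = 0.3 | ρ = 0.5 | ρ = 0.7 |
|---|---|---|---|---|
| 3, 6, 12 months | gone by 12 months | 55% | 71% | 91% |
| 3, 6, 12 months | sustained | 5% | 5% | 5% |
| plus one pre-randomisation level | gone by 12 months | 64% | 80% | 96% |
| plus one pre-randomisation level | sustained | 68% | 83% | 97% |
| plus two pre-randomisation levels | gone by 12 months | 66% | 82% | 97% |
| plus two pre-randomisation levels | sustained | 85% | 95% | 99.8% |

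Simulation (4,000 trials per setting, ρ = 0.5 and 0.7) agrees for the settings with three and four levels. An unadjusted 12-month contrast at 5% rejects in about 80% of trials with a sustained benefit and about 5% with a faded one.

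**Step 3: Bonferroni on the 12-month contrast.** Baseline adjustment divides the error variance by 1/(1 − ρ²), so the noncentrality is d × √(n/2) / √(1 − ρ²).

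| Alpha | Unadjusted | Baseline-adjusted, ρ = 0.3 / 0.5 / 0.7 |
|---|---|---|
| 0.05 | 80% | 84 / 90 / 98% |
| 0.05/3 = 0.0167 | 66% | 70 / 80 / 94% |
| 0.05/4 = 0.0125 | 62% | 67 / 77 / 92% |

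**The case against.** **The sustained-benefit result depends on the time levels.** A reader might infer that the planned test is bound to miss a lasting benefit. The article does not support that as a general claim. The 5% figure needs 3, 6 and 12 months to be the only levels. The accelerometry schedule and the baseline covariate imply this, but Table 1, the Outcomes section and the abstract put MVPA at the post-supervised visit too. That visit precedes randomisation, so using it as a level gives a sustained benefit an interaction to detect. This objection stands and makes that half of the point conditional. It does not touch the faded-benefit half.

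**A 12-month comparison is planned.** The abstract compares groups at each time point, and the statistics section does not make 12-month inference conditional on the interaction. A reader might infer a gatekeeping sequence, or that a significant interaction alone decides the trial; neither is stated. If a 12-month contrast at 0.05/3 did follow a significant interaction, simulation with three levels shows a faded effect claimed at 12 months in only about 1% of trials, but a sustained one in only about 3%. So that sequence would cure one error and leave the other.

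**The Bonferroni loss can be overstated.** The plan adjusts for baseline. At ρ of about 0.5 or more, three-visit Bonferroni leaves power at about 80% or above. The article also defines no family. The 66% and 62% figures apply only to the unadjusted contrast.

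**It is a summary sentence in a condensed article.** True, and an analysis plan may settle it. But the statistics section fits the same interaction and names no other primary test, so nothing in the article corrects the abstract.

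**Conclusion.** The mismatch is in the text and holds. The test named as formal does not test the 12-month hypothesis under any reading of the time levels. A benefit gone by 12 months gives a significant interaction in 55–91% of trials with levels 3, 6 and 12 months, and in 64–97% with one or two pre-randomisation levels added.

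That a sustained benefit is detected only 5% of the time is conditional: it holds for the 3-, 6- and 12-month reading. With the post-supervised visit as a level, the figure is about 68–97%. The passages on when MVPA is measured must be reconciled before either figure can be called the plan's.

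If Bonferroni covers the 12-month contrast over three or four visits, its power falls from 80% to 66% or 62% unadjusted, or from 84–98% to 70–94% or 67–92% baseline-adjusted.

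All percentages are illustrative. They rest on a back-solved d of 0.41, an assumed ρ of 0.3 to 0.7, two-sided testing, 94 evaluable per arm, and a linear fade for the faded pattern. The mismatch itself needs none of these.

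**What to change.** State one primary test: the model-estimated between-group difference in MVPA at 12 months, from the mixed model with post-randomisation visits as responses and pre-randomisation MVPA as a covariate, at two-sided 5%. Say that it is not gated by the interaction and lies outside the Bonferroni set. Make the interaction and the 3- and 6-month contrasts secondary, and limit Bonferroni to those. Amend the abstract sentence to match.

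In the same edit, reconcile the accelerometry schedule with Table 1, the Outcomes section and the abstract on whether MVPA is measured at the post-supervised visit, and list the levels of the time factor.

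The cost is wording only: the same data, model family and sample size.

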**Discussion:**

If successful, peer support may be proposed, adopted and implemented as a strategy to encourage cancer survivors to maintain exercise beyond the duration of a short-term, supervised intervention. A peer support-exercise model has the long-term potential to reduce comorbidities, improve physical and mental wellbeing, and significantly reduce the burden of disease in cancer survivors.

**Ethics:**

Human Research Ethics Committee of Bellberry Ltd. (#2015–12-840).

**Trial registration:**

Australian New Zealand Clinical Trial Registry 12618001855213. Retrospectively registered 14 November 2018.

Trial registration includes all components of the WHO Trial Registration Data Set, as recommended by the ICMJE.

## Strengths and limitations of this trial

This is the first randomised controlled trial to investigate the effectiveness of peer support for maintaining physical activity following a brief supervised training intervention in cancer survivors.This trial will monitor changes in physical activity, physical fitness, body composition, blood markers of health, and indicators of quality of life for 12-months.If peer support is found to improve maintenance of exercise for 12 months following a brief supervised training intervention, it will emerge as an effective means to improve the health and wellbeing of people living with and beyond cancer.The applications of this trial will be limited to people living with and beyond breast, colon and/or prostate cancer.

## Background

Cancer incidence is rapidly increasing with an estimated 18.1 million new cases and 9.6 million cancer deaths worldwide in 2018 [1]. Whilst two thirds of all people diagnosed with cancer survive at least 5 years, many live with reduced functional capacity, poor health-related quality of life and high levels of fatigue [2, 3]. Clinically significant cancer treatment-related adverse effects can last for up to 10 years post-diagnosis; the enduring nature of such effects highlights the need for long-term management strategies to improve outcomes following diagnosis and treatment for people with cancer [4, 5].

Higher levels of physical activity (PA) is associated with a reduced risk of cancer recurrence [6], with an estimated 30–40% risk reduction for both breast and colorectal cancer survivors [7, 8]. Emerging and accumulating evidence also shows that PA may reduce the risk of prostate cancer recurrence [9]. Moreover, exercise interventions for cancer patients and survivors has also been shown to reduce cancer-related fatigue [10], and improve psychological wellbeing and quality of life [11], physical function [12], body weight and composition [13], muscle strength and endurance [12], immune function [14], and cardiorespiratory fitness [15].

A growing body of research shows that relatively high intensity exercise can elicit rapid and significant improvements in various markers of health across a range of different clinical populations [16–18]. Devin et al. (2016) recently showed that 4 weeks of high intensity interval training (HIIT) significantly increased cardiorespiratory fitness ($$ \dot{\mathrm{V}}{\mathrm{O}}_{2\mathrm{peak}} $$, + 3.5 mL.kg^− 1^.min^− 1^; *p* < 0.001) and led to significant decreases in fat mass (− 0.74 kg; *p* < 0.002) and increases in lean mass (+ 0.72 kg; *p* < 0.001) in colorectal cancer survivors [19]. These results are clinically meaningful when placed in the context of the Cooper Centre Longitudinal Study results which estimated that an increase in $$ \dot{\mathrm{V}}{\mathrm{O}}_{2\mathrm{peak}} $$ of 3.5 mL.kg^− 1^.min^− 1^ was associated with a 10% (hazard ratio, 0.90 95% confidence interval [CI] [0.84–0.97]) decrease in cancer-specific mortality risk [20]. Importantly, three HIIT sessions per week, each comprising only 16 min of high intensity exercise interspersed with active recovery, allowed participants to meet the ‘cardiovascular’ component of the current exercise oncology guidelines (150 min per week of moderate or 75 min per week of vigorous aerobic exercise or an equivalent combination) [21, 22]. In addition to HIIT being a time-efficient, highly effective means of rapidly improving health, Kampshoff et al. [23] have recently reported that high intensity exercise, when compared to low-to-moderate intensity exercise, results in greater improvements in quality of life. When these findings are considered with those of Martin et al. [24], who found that higher intensity exercise helps cancer survivors maintain their motivation to exercise, the available, emerging research indicates that HIIT holds potential for addressing the long-term health of cancer survivors.

Despite the strong body of evidence showing the benefits of PA and exercise for cancer survivors, research suggests that very few cancer survivors meet the exercise oncology guidelines [25–27]. Indeed, some studies have shown that cancer survivors are less active than those who have not had cancer [28]. For example, Galvao et al. [26] reported only 12% of prostate cancer survivors meet the current exercise oncology guidelines [21]. In addition, Gomersall et al. [29] found that less than 25% of participants who start a physical activity program remain active after 6 months [30]. Similarly, Courneya et al. [31] found that without support, only 36% of patients with lymphoma met exercise oncology guidelines 6 months following an intervention. These results substantiate the colloquially-known ‘drop-off’ in PA participation following the completion of PA interventions and may explain the typically poor maintenance of health outcomes at longer-term follow-up assessments post-intervention.

Maintaining exercise adherence and its subsequent health benefits following supervised exercise interventions is therefore an area of particular need in exercise oncology [2, 32]. To date, variations of support for improving and maintaining the activity levels of cancer survivors have included phone, text reminders and printed materials [33]. Although these methods of behavioural support have shown efficacy in cancer populations in the short to mid-term [34, 35], they also have some inherent limitations, with the most prominent being a lack of face-to-face interaction.

Peer support, which is underpinned by components of social cognitive theory [36] and the theory of planned behaviour [37], uses trained individuals who have shared experiences and who provide knowledge, emotional, social and/or practical help to support others. Though peer support has been used to maintain physical activity levels in patients recovering from cardiac surgery [38], its effectiveness as a means of promoting and/or maintaining physical activity in cancer survivors following a brief supervised intervention warrants further investigation [39]. To date, interventions have seen promising increases in PA among peer-supported cancer survivors compared to contact controls [40, 41]. However, these trials were conducted solely with female breast cancer survivors. Thus, the generalizability of the findings to survivors of other cancers and male cancer survivors remains unknown. In addition, these interventions were solely telephone-based despite interactive mediums of intervention delivery (e.g. face-to-face delivery) being particularly important for people in the early stages of behaviour change [42]. Furthermore, these interventions were relatively short, with support lasting only 12 weeks. Therefore, the durability of these findings remains unknown.

The primary aim of this trial is to evaluate the influence of peer support compared to no peer support on MVPA 12 months following a brief supervised exercise intervention in cancer survivors. Secondarily, this trial aims to determine the influence of peer support on various exercise-related markers of health (cardiorespiratory fitness, body composition, strength, quality of life, blood biomarkers, overall physical activity and sedentary behaviour) 12 months following a brief supervised exercise intervention in cancer survivors compared to those without peer support. It is hypothesised that peer support will result in higher levels of MVPA and markers of health 12 months follow a brief supervised exercise intervention compared to those without peer support.

## Methods

### Study design

This two-arm randomised controlled trial will involve men or women with a previous diagnosis of breast, colorectal or prostate cancer. All participants and peer supporters will first complete 4 weeks (12 sessions) of HIIT supervised by Accredited Exercise Physiologists (AEP) at the School of Human Movement and Nutrition Sciences, The University of Queensland, Brisbane, Australia (‘supervised phase’). On completion of the supervised phase, participants will be stratified by gender and age before being randomly assigned (1:1) to either a peer support group or a non-peer support group. All will be provided with written recommendations to maintain three HIIT sessions per week, or an alternative equivalent that meets the exercise oncology guidelines (i.e. 150 min per week of moderate or 75 min per week of vigorous aerobic exercise or an equivalent combination), for 12 months [21, 22]. Those assigned to the peer support group will have access to a peer who will provide support to meet the HIIT and/or exercise guidelines.

All participants will complete a series of assessments (see Table 1) at baseline, at the end of the supervised phase, and at 3-, 6- and 12-months following the supervised phase (see Fig. 1).

**Table 1 Tab1:** Schedule of data collection

Assessment or Outcome	Study Period						
*Time Point:*	*Pre-FM*	*FM*	*Pre-SP*	*Post-SP*	*3 M*	*6 M*	*12 M*
*Screening*							
Participant eligibility	✓						
Adult Pre-Exercise Screening System	✓						
Informed consent	✓						
Doctor’s consent	✓						
Medical history and current status	✓	✓	✓	✓	✓	✓	✓
Demographics	✓						
Concomitant research study participation	✓	✓	✓	✓	✓	✓	✓
*Primary Outcomes*							
Moderate-to-vigorous physical activity (MVPA)			✓	✓	✓	✓	✓
*Secondary Outcomes*							
Cardiorespiratory fitness ($$ \dot{\mathrm{V}}{\mathrm{O}}_{2\mathrm{peak}} $$)		✓	✓	✓	✓	✓	✓
Body composition (DXA)			✓	✓	✓	✓	✓
Anthropometry (BMI)			✓	✓	✓	✓	✓
Strength (isometric grip strength)			✓	✓	✓	✓	✓
Blood biomarkers (IL-6, IL-8, Hepcidin, TNF-α, IGF-1, IGF-2, IGFBP-3 and CRP)			✓	✓	✓	✓	✓
Self-reported physical activity (Godin)			✓	✓	✓	✓	✓
Sedentary behaviour and light physical activity (accelerometry)			✓	✓	✓	✓	✓
Quality of life and wellbeing (EORTC QLQ C-30, SF-36 and FACT-G)			✓	✓	✓	✓	✓
Cancer-related fatigue (FACIT-F)			✓	✓	✓	✓	✓
Insomnia (ISI)			✓	✓	✓	✓	✓
Symptom distress (BSI)			✓	✓	✓	✓	✓
Depression and anxiety (DASS, PHQ-9 and GAD-7)			✓	✓	✓	✓	✓
Participant:peer supporter relationship (Therapeutic Alliance)			✓	✓	✓	✓	✓
Self-efficacy			✓	✓	✓	✓	✓
Barriers and enablers to PA			✓	✓	✓	✓	✓
Tertiary Outcomes							
Semi-structured interviews							✓
Physical activity preferences			✓	✓	✓	✓	✓
Economic evaluation (AQoL-8D)			✓	✓	✓	✓	✓
Adverse and serious adverse events		✓	✓	✓	✓	✓	✓

*Key: Pre-FM* pre-familiarisation, *FM* familiarisation, *Pre-SP* pre-supervised phase, *Post-SP* post-supervised phase, *3 M* 3-months post-randomisation testing, *6 M* 6-months post-randomisation testing, *12 M* 12-months post-randomisation testing, $$ \dot{\mathrm{V}}{\mathrm{O}}_{2\mathrm{peak}} $$ peak volume of oxygen consumption, *DXA* dual energy X-ray absorptiometry, *BMI* body mass index, *IL-6* interleukin 6, *IL-8* interleukin 8, *TNF-α* tumour necrosis factor – alpha, *IGF-1* insulin-like growth factor 1, *IGF-2* insulin-like growth factor 2, *IGFBP-3* insulin-like growth factor-binding protein 3, *CRP* C-reactive protein, *Godin* Godin Leisure-Time Physical Activity Questionnaire, *EORTC QLQ C-30* European Organization for Research and Treatment of Cancer quality of life questionnaire for people with cancer, *SF-36* Short form 36 health survey, *FACT-G* Functional Assessment of Cancer Therapy: General, *FACIT-F* The Functional Assessment of Chronic Illness Therapy: Fatigue, *ISI* Insomnia Severity Index, *BSI* Brief Symptom Inventory, *DASS* Depression Anxiety Stress Scale, *PHQ-9* Patient Health Questionnaire-9, *GAD-7* Generalised Anxiety Disorder 7-item scale, *PA* physical activity, *AQoL-8D* Assessment of Quality of Life – 8 Dimensions Multi-Attribute Utility Instrument

